### Secondary outcome measures

The secondary outcome measures include BP (SBP and DBP) and QOL. Participants’ QOL will be assessed using the World Health Organization Quality of Life Scale (WHOQOL-BREF). The WHOQOL-BREF, was developed specifically for patients with SCI to evaluate QOL and is the most widely used questionnaire [24], with adequate reliability and validity [24,25]. It consists of 26 items measuring four domains: physical health, mental health, social relationships, and environment. Each item is ranked on a 5-point Likert scale. The higher the scores the better the QOL [24]. Participants will be instructed to consider their experiences over the previous 15 days when responding to the questionnaire items.

### Data analysis

All statistical analyses will be conducted on IBM SPSS Statistics version 24.0 (IBM Co., Armonk, NY, USA), with a significance level at 0.05.

Descriptive statistics of means and standard deviations will be used to summarize continuous variables, while frequencies and percentages will be used for categorical variables. Data distribution will be assessed statistically using the Kolmogorov–Smirnov and Shapiro–Wilk tests, and visually through histograms, Q-Q plots, and box plots. Baseline comparisons of continuous variables between groups will be conducted using independent *t-*test while the chi-square (χ²) test will be used for categorical variables. For normally distributed data, a mixed model analysis of variance (ANOVA) with a 2 x 3 design (treatment group [ULAE group versus control group] x time [baseline, 8-week post-intervention, and 14-week follow-up]) will be employed to evaluate treatment effectiveness. The treatment group (between-subject factor) will be treated as a fixed effect, while time (within-subject factor) will be treated as a random effect. For non-normally distributed data, the Mann–Whitney *U* test will be used. Potential confounding variables, such as sex, education level, BMI, duration of injury, and type of injury will be adjusted for in the analysis. The intention to treat (ITT) principle will be applied, with all randomized participants included in the analysis according to their originally assigned treatment groups, regardless of whether they completed treatment.

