### Hypotheses

The primary hypothesis is that participants receiving ULAE plus general exercise will demonstrate greater improvements in RPP and functional independence compared to those receiving general exercise alone at 8 weeks post-intervention and at the 14 weeks follow-up. The secondary hypothesis is that participants receiving ULAE plus general exercise will demonstrate greater improvements in BP and QOL compared to those receiving general exercise alone at 8 weeks post-intervention and at the 14 weeks follow-up.

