### Sample size calculation

To our knowledge, no previous study has evaluated the effects of ULAE plus general exercise program compared to general exercise alone among SCI patients, using the RPP (product of SBP and HR) as an outcome. However, since the minimal clinically important difference (MCID) for total Spinal Cord Independence Measure III (SCIM III) has been reported to be 10.0 points [17], this study was powered to detect a minimum difference of 10% points between the ULEA group and control group (assuming a standard deviation [SD] of 12.0, based on the study by Akkurt et al. [15]. Using the following parameters— F-test, repeated measures, between-subjects analysis of variance (ANOVA); alpha (*α*) level of 0.05; power of 0.80; effect size of 0.40 when accounting for 3 repeated measures; and correlation among repeated measures of 0.5— a total of 36 participants was required. Accounting for a potential dropout rate of 30% (n = 10), the final sample size was determined to be 46 participants. Calculations were performed using G Power 3.1.9.2 software [18].

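### Time, meaning three pre-set visits, is declared a random effect in the primary ANOVA; this contradicts the hypotheses and the sizing test and leaves the error term of the treatment test open

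*Protocol article*

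**What the plan says.** All references are to the protocol article.

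- **Data analysis.** For normally distributed data, treatment effectiveness is evaluated by "a mixed model analysis of variance (ANOVA) with a 2 x 3 design", the factors being group and time (baseline, 8 weeks, 14 weeks). Each factor is then given a status: "The treatment group (between-subject factor) will be treated as a fixed effect", "while time (within-subject factor) will be treated as a random effect". Testing is "with a significance level at 0.05". If data are not normal, the Mann-Whitney test replaces the ANOVA.
- **Hypotheses.** The primary hypothesis is that the ULAE arm improves more on rate pressure product and functional independence "at 8 weeks post-intervention and at the 14 weeks follow-up".
- **Sample size calculation.** N = 36 comes from a repeated-measures F test of the between-subjects effect, with "power of 0.80; effect size of 0.40 when accounting for 3 repeated measures" and "correlation among repeated measures of 0.5". The target is a 10-point SCIM III difference with SD 12.

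**The concern.** A factor is random when its levels stand for a larger population of levels. Here the three visits are fixed by design, and the inference is about two of them. Declaring them random changes the question to a group effect averaged over hypothetical visits.

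It also changes the error term. In a repeated-measures design the random unit is the participant, and the sizing test relies on that. With time random, the usual convention makes group x time random too, so it enters the denominator of the group test. In a randomised trial no difference is expected at baseline, so a real treatment effect appears partly as group x time. It then inflates the denominator of the test meant to detect it. If an analyst also takes the sentence as the full list of random terms, three correlated readings per person are handled as independent.

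**Working it through.** **Inputs.** From Sample size calculation: difference 10, SD 12, correlation rho = 0.5, f = 0.40, m = 3 measures, N = 36, power 0.80. From Data analysis: alpha 0.05. Assumptions: 18 per arm (no ratio is stated), equal correlation between all visits, complete data. Two patterns of group difference over baseline, 8 and 14 weeks are used: 10/10/10 and 0/10/10.

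**1. The plan's own figure.** For the between-subjects test with a participant error term, lambda = f² N m / [1 + (m − 1) rho] on (1, N − 2) df. At N = 36, lambda = 0.16 × 36 × 3 / 2 = 8.64 and power is 0.815. At N = 34 power is 0.791. So 36 is the smallest even N reaching 0.80, and it reproduces with participants as the error term.

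**2. Expected mean squares with no treatment effect (SD² = 144).**
- Group, and participants within group: 144 × (1 + 2 × 0.5) = 288
- Group x time, and the within-participant residual: 144 × (1 − 0.5) = 72
- Residual when participant is left out: 144

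**3. Literal fit, no participant term.**
- Group against the residual: the ratio is 288/144 = 2 where it should be 1. P(|Z| > 1.96/√2) = 0.166; simulation gives 0.168 (0.121 at rho 0.3, 0.228 at rho 0.8).
- Group against group x time on (1, 2) df: the ratio is 288/72 = 4. P(F > 18.51/4) = 0.164; simulation gives 0.166 (0.105 to 0.354 over rho 0.3 to 0.8).
- Group x time against the residual: the ratio is 72/144 = 0.5, so the test is conservative. Simulated type I error is 0.004.

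**4. Participant term kept, time and group x time random.** The denominator for group becomes MS(participant) + MS(group x time) − MS(residual), a quasi-F with approximate df. Simulated type I error is 0.048 (0.041 to 0.049 over rho 0.3 to 0.8). For 0/10/10 the mean difference is 6.67, and the group differences deviate from it by −6.67, 3.33 and 3.33. The interaction sum of squares is (18/2) × (44.4 + 11.1 + 11.1) = 600, which adds 600/2 = 300 to MS(group x time), taking it from 72 to 372. The effect therefore sits in its own denominator.

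**5. Rejection rates (20,000 simulated trials per setting, N = 36, rho 0.5).**

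| Test | No effect | 10/10/10 | 0/10/10 |
|---|---|---|---|
| Group, participant term, time fixed | 0.050 | 0.845 | 0.512 |
| Group, participant term, time and group x time random | 0.048 | 0.804 | 0.127 |
| Group vs residual, no participant term | 0.168 | 0.952 | 0.730 |
| Group vs group x time, no participant term | 0.166 | 0.798 | 0.069 |
| Group x time, participant term, time fixed | 0.048 | 0.050 | 0.717 |
| Group x time, no participant term | 0.004 | 0.004 | 0.337 |

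At N = 46 with complete data the inflated type I errors hardly move (0.169 and 0.167).

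**The case against.** The strongest reply is that this is a misused term and not a plan to ignore within-person correlation. The same sentence labels group a between-subject and time a within-subject factor, labels that in a standard mixed ANOVA imply a participant error stratum. The sizing test uses that stratum too. A condensed article need not list every random term, so the absence of a named participant effect is not itself a fault.

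This largely stands. A reader might infer that the group test will use the wrong error term, so that the trial's type I error is inflated. The documents do not support that as a fact: with the implied participant term the rate stays near 5%. The inflation holds only if the sentence is fitted literally.

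Four further limits are fair:
- The direction depends on the test. The literal fit makes the group test too liberal and the group x time test too strict, and the section does not say which of them carries the treatment effect.
- The severe power losses belong to the 0/10/10 pattern. For 10/10/10, with the participant term kept, power falls only from 0.845 to 0.804.
- The 51% under fixed time is itself low because baseline dilutes the group main effect. Random time does not cause that.
- The ANOVA applies only to outcomes judged normal.

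The reply does not rescue the statement about time. That is a positive model statement, not missing detail, and it remains wrong when the participant term is present.

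**Conclusion.** The concern holds in a conditional form. Declaring time random is an error: it conflicts with hypotheses about two named visits and with the test that produced N = 36. Its cost depends on implementation, under SD 12, correlation 0.5, 18 per arm and complete data:

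- **No participant term:** group-test type I error about 16-17%. Group x time type I error about 0.4%, with power about 34% instead of 72% for 0/10/10.
- **Participant term kept, time and group x time random:** type I error near 5%, but group-test power for 0/10/10 about 13% against 51%.

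The model serves both primary outcomes whenever they are judged normal, so the wording should be settled before the analysis is run. The error rates are computed on the SCIM III inputs. The protocol gives none for rate pressure product, but the type I error rates do not depend on the SD.

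**What to change.** Replace the sentence on fixed and random effects with: *Group, visit (categorical) and group x visit will be fixed effects, with participant as the random effect (or an equivalent within-participant covariance), and the treatment effect will be the between-group contrasts at 8 and 14 weeks.*

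Both time points should stay in the primary question, because the primary hypothesis covers both; making 14 weeks secondary would change the trial's objective. The estimation method, the df method and the choice of covariance structure can be left to the statistical analysis plan.

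The cost is one sentence of wording, with no added data or participants. The change restores the participant-based error structure used for sizing. The protocol says that amendments will be communicated to the ethics committees and updated in the registry, so this one should follow that route.

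### A normality test of the data decides whether the treatment comparison becomes a Mann–Whitney U test, which cannot carry the promised covariate adjustment and is not the analysis the trial was sized for

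*Protocol article*

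**What the plan says.** In the protocol article, under Data analysis, the steps are these:

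- The distribution is checked first: "Data distribution will be assessed statistically using the Kolmogorov–Smirnov and Shapiro–Wilk tests", together with histograms, Q-Q plots and box plots. The object of the check is the data. Model residuals are not mentioned.
- Normal data go to a mixed ANOVA, group (2) by time (3), with baseline as one of the three time levels.
- Otherwise: "For non-normally distributed data, the Mann–Whitney" U test is to be used. The section does not say whether the week-8 value, the week-14 value or a change score is ranked.
- Sex, education level, BMI and then "duration of injury, and type of injury will be adjusted for in the analysis". No branch is exempted.

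Under Sample size calculation, the only test used for sizing is a between-subjects repeated-measures ANOVA. It rests on the SCIM III MCID of 10 points, and 36 participants are required before the dropout allowance.

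**The concern.** Three things are at stake.

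1. **The covariate promise cannot be kept in one branch.** A Mann–Whitney U test compares one value per person between two groups. It has no place for the five listed covariates and no group-by-time term, although the Hypotheses section claims effects at both week 8 and week 14.
2. **The data choose the estimand.** In one branch the result is a difference in means, which can be read against the 10-point MCID. In the other it is a rank comparison with no adjusted mean difference. RPP and SCIM III, the two primary outcomes, could end up with different kinds of result.
3. **The wrong thing is tested.** SCIM III is bounded from 0 to 100, and participants have injuries anywhere from C7 to L5. Raw scores from so mixed a group can look non-normal while the residuals of an adjusted model are acceptable. The check can therefore trigger the switch when the linear model needs no rescue.

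**Working it through.** **Inputs (Sample size calculation).** "level of 0.05; power of 0.80"; "effect size of 0.40 when accounting for 3 repeated measures"; "correlation among repeated measures of 0.5"; a 10-point difference with "assuming a standard deviation [SD] of 12.0". From the last two, d = 10/12 = 0.833 and f = d/2 = 0.417. The stated f = 0.40 corresponds to d = 0.80, which is used below. The allocation ratio is not stated; 1:1 is assumed, so 18 per arm at N = 36.

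**Step 1: reproduce the protocol's figure.** For the between-subjects factor with m measures,

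λ = f²·N·m / (1 + (m − 1)ρ) = 0.16 × 36 × 3 / (1 + 2 × 0.5) = 17.28 / 2 = 8.64.

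On 1 and 34 degrees of freedom at 0.05 this gives power 0.815. N = 34 gives 0.791, so 36 is the smallest even N that reaches 0.80. The figure reproduces.

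**Step 2: the fallback, same inputs, normal data, one visit.** The large-sample efficiency of Mann–Whitney relative to the t-test is 3/π = 0.955, so 18 per arm acts like 17.19. The noncentrality is 0.80 × √(17.19/2) = 2.35, and power is 0.62. Simulation (2,000 runs) gives 0.61.

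Change scores do not help at this correlation. Their variance is 2(1 − ρ) = 2 × 0.5 = 1 times that of a raw score, so d is unchanged. Simulation gives 0.62.

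**Step 3: baseline-adjusted alternatives, N = 36.**
- Single-visit ANCOVA: residual SD factor √(1 − 0.5²) = 0.866; d becomes 0.80/0.866 = 0.924; noncentrality 0.924 × √(18/2) = 2.77; power 0.77.
- Baseline-adjusted mean of weeks 8 and 14: the variance of the mean is (1 + 0.5)/2 = 0.75 and its covariance with baseline is 0.5, so the residual variance is 0.75 − 0.25 = 0.50. Then d becomes 0.80/0.707 = 1.13, the noncentrality is 1.13 × 3 = 3.39, and power is about 0.91 (simulated 0.90).

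**Step 4: other sample sizes.**

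| N | Sizing formula | Mann–Whitney, one visit | Gap |
|---|---|---|---|
| 32 (46 less 30%) | 0.76 | 0.57 | 0.19 |
| 36 | 0.815 | 0.62 | 0.19 |
| 46 | 0.90 | 0.74 | 0.17 |

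Gaps are taken from unrounded values. With d = 0.833 instead of 0.80, the Mann–Whitney figures are 0.60, 0.66 and 0.77.

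**Step 5: two checks on the comparator (N = 36, effect at weeks 8 and 14 only, simulated).**
- Normal data: the mixed ANOVA's group-by-time test has power 0.67, against 0.61 for Mann–Whitney. The gap is 6 points.
- Skewed data (lognormal, sigma 0.5, an assumption): in two sets of runs Mann–Whitney at week 8 has 0.76 to 0.80 and single-visit ANCOVA 0.74 to 0.77. The baseline-adjusted mean of both visits has 0.89 to 0.90. The group-by-time test, from one set, has 0.66.

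**Step 6: how often normal data might trigger the switch.** The article gives no rule for which arms or visits decide. As an illustration only, with independent 5% tests: two arms at one visit, 1 − 0.95² = 0.10; all six arm-by-visit cells with any rejection counting, 1 − 0.95⁶ = 0.26.

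**The case against.** The strongest reply is that the power loss is mostly a matter of what Mann–Whitney is compared with. The protocol plans no ANCOVA. Its other branch is a mixed ANOVA with baseline as a time level, and against that model's group-by-time test the loss is about 6 points. The 0.815 comes from a formula that treats the group difference as present at all three measurements, baseline included. Ranking itself costs little: an unadjusted t-test on the same week-8 values has power 0.645, about 2 points above Mann–Whitney. And the fallback is meant for non-normal data, where, under the skew tried, it does at least as well as single-visit ANCOVA. All of this stands, and it limits the size that can be claimed.

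Some stronger readings are tempting but not supported:

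- **That the fallback cannot use baseline.** Change scores can be ranked, and the article does not say which value enters the test. At the stated correlation of 0.5 this gains almost nothing. A larger loss computed on raw values at a higher correlation would rest on an input the protocol does not give, and ranking change scores would then recover most of it.
- **That about a quarter of normal data sets would be switched.** That needs a six-cell rule the article does not state, and it ignores the plots that accompany the tests.
- **That type I error is inflated.** Simulated Mann–Whitney size under normality was about 0.04.
- **That no mean difference could be reported at all.** Means and standard deviations are planned as descriptive summaries. What is lost is an adjusted difference that belongs to the test.
- **That the fallback alone breaks the intention-to-treat statement.** No missing-data method is given for either branch.

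None of this removes the conflict between the two sentences. It is in the stated text and is not a detail left to another document.

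**Conclusion.** The point holds as an inconsistency in the stated analysis, with a power cost that depends on the comparator. If the fallback is triggered, the covariate adjustment, the group-by-time comparison and an adjusted difference to read against the MCID are all lost, and the analysis is no longer the one used for sizing.

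At the protocol's own inputs, a single-visit Mann–Whitney test has power of about 0.62 at N = 36: about 19 points below the planning figure, about 15 below single-visit ANCOVA, and nearly 30 below a baseline-adjusted analysis of both follow-up visits. These figures assume normal data, equal arms, d = 0.80 and correlation 0.5. Only the last comparison goes against the rank test in both settings tried. Under the assumed skew it still trails by roughly 10 to 13 points. A reader should not infer that the rank test is always the weaker choice; the case against the switch does not need that.

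**What to change.** Delete the switch. In its place, name one longitudinal linear model for SCIM III, RPP, BP and QOL, to be used whatever the normality tests show:

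- the week-8 and week-14 values as outcomes;
- group, visit and group-by-visit as terms;
- the baseline value and the listed covariates as adjusters.

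Report the adjusted mean difference with its confidence interval, and for SCIM III read it against 10 points. Check the model's residuals graphically. Keep a bootstrap interval for the same difference, an analysis of log RPP, or a rank-based test as sensitivity analysis only.

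The cost is wording and one extra sensitivity analysis; no new participants, visits or data are needed. The downside is that this changes the stated primary model, since the present mixed ANOVA carries baseline as a time level. It must therefore be fixed before any unblinded analysis and recorded as an amendment with the ethics committees and the registry, as the Ethical consideration section already provides.

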## Introduction

Spinal cord injury (SCI) is a devastating injury accompanied by physical, psychosocial, and economic problems, as well as significant personal and social repercussions [1]. It is often associated with distinct diverse secondary complications including acute complications such as bradyarrhythmias, hypotension, impaired temperature, pain, spasticity, and autonomic dysreflexia [2] and chronic complications such as cardiopulmonary, intestinal, urinary bladder, and sexual disorders [3]. Long-term secondary complications can increase morbidity and negatively impact functional independence, community participation, and quality of life (QOL) [3]. Additionally, individuals with SCI, depending on their type of injury, often experience reduced physical activity levels, which is considered antecedent to development of various complications [4]. Individuals with SCI are approximately 40% less physically active compared to able-bodied counterparts [5].

A major complication linked to physical inactivity in individuals with SCI is the increased prevalence and earlier onset of cardiovascular disease (CVD) [6]. Research suggests that individuals with SCI, particularly those with cervical and thoracic levels of injury, often struggle with unstable blood pressure (BP), leading to persistent hypotension and episodes of uncontrolled hypertension [7].

Following SCI, there is an immediate disruption in connections between supraspinal structures and sympathetic preganglionic neurons. This leads to instability, causing spinal circuits to solely regulate sympathetic activity, which impacts BP control. Acute SCI, particularly at the cervical level, often results in severe hypotension and persistent bradycardia, contributing to neurogenic shock. However, the recognition and management of these cardiovascular dysfunctions following SCI pose significant clinical challenges. Moreover, CVD in both the acute and chronic stages of SCI is among the most common causes of mortality in this population [8].

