### Study settings

The study is being conducted in the outpatient unit of the Physiotherapy Department at each of the three major healthcare facilities in Kano State, northern Nigeria: AKTH, Murtala Mohammed Specialist Hospital (MMSH), and NOHD.

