### Inclusion criteria

To be eligible for the study, participants must meet the following criteria:

Received medical clearance from their physicians confirming they are fit to participate in exercise.Male or female aged 18–65 years old.Diagnosed with traumatic SCI between the 7^th^ cervical (C7) and 5^th^ lumbar (L5) vertebrae, with a minimum of 3 months post-injury.Upper limb muscle power of at least 3, as assessed by gross muscle power testing, to be able to propel an arm crank ergometer.Willing to participate and having provided signed informed consent.

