### Randomization and blinding

After ensuring study eligibility and completing baseline assessments, the participants will be randomly assigned to either ULAE plus general exercise group or general exercise alone (control) group. Randomization will be performed by an independent person (a record officer) at each study site using computer-generated random numbers. To ensure allocation concealment, sequentially numbered, opaque, sealed envelopes will be prepared in accordance with the generated random sequence. Upon the availability of an eligible participant at the scheduled appointment, the next envelope will be opened to determine the intervention group to which the participant is allocated. Outcome assessors will be blinded to group allocation. However, owing to the nature of the study interventions, blinding of the physiotherapists administering treatment will not be possible. Unbinding will only be permissible in cases where a participant experiences a serious adverse event or after the study’s completion.

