### Baseline data collection

Sociodemographic and clinical characteristics, including age, sex, marital status, education level, occupational status, height, weight, body mass index (BMI), duration of injury, type of injury, level of affectation, and presence of comorbidities will be collected. American Spinal Injury Association (ASIA) Impairment Scale will be used to classify the level of injury [20]. Each participant will be assigned a unique ID for anonymity and tracking purposes.

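### The primary model uses the baseline outcome only as a time level and adjusts for an open covariate list that names neither study site nor injury level

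*Protocol article*

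**What the plan says.** - **Model.** The Data analysis section of the Protocol article specifies a mixed 2 x 3 ANOVA of treatment group by "time [baseline, 8-week post-intervention, and 14-week follow-up". Baseline is thus a level of the within-subject factor. The section does not say which term, group or group-by-time, is the treatment test.
- **Adjustment.** The same section says: "Potential confounding variables, such as sex, education level, BMI, duration of injury, and type of injury will be adjusted for in the analysis". It also plans t-tests and chi-square tests comparing the arms at baseline.
- **Site.** Randomization and blinding says: "Randomization will be performed by an independent person (a record officer) at each study site using computer-generated random numbers". Study settings places the trial at "each of the three major healthcare facilities in Kano State, northern Nigeria". Site is not named in the analysis.
- **Injury level.** Baseline data collection records level separately from type: "duration of injury, type of injury, level of affectation, and presence of comorbidities will be collected". Only type is named for adjustment. Inclusion criteria admit a wide range: "Diagnosed with traumatic SCI between the 7^th^ cervical (C7) and 5^th^ lumbar (L5) vertebrae". The Introduction says that patients with SCI, "particularly those with cervical and thoracic levels of injury, often struggle with unstable blood pressure".
- **Sizing.** Sample size calculation says "this study was powered to detect a minimum difference of 10% points between the ULEA group and control group", with SD 12.0, and uses a between-subjects repeated-measures F test (effect size 0.40, three measures, correlation 0.5, alpha 0.05, power 0.80), giving 36 evaluable participants and 46 after an allowance for dropout.

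**The concern.** With about 36 evaluable participants, how the baseline outcome enters the model largely decides the precision. As a covariate it removes the predictable part of the follow-up value. As a time level it gives either a change-from-baseline comparison, which is less efficient, or, if the group main effect is read, an average that includes a visit at which no difference is expected.

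The covariates chosen are a second matter. Education level and BMI are named. The unit within which allocation is run is not, nor is the characteristic that the Introduction links to unstable blood pressure, although systolic pressure is a component of a primary outcome (rate pressure product). Because the covariates are given as examples, the adjusted primary model is not fixed, and several different adjusted answers would all fit the text. The baseline significance tests add a possible route to choosing covariates on chance imbalance.

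**Working it through.** **Inputs.** From Sample size calculation: difference 10 SCIM III points (the text's 10% points, read as 10 on a 100-point scale), SD 12, correlation 0.5, N = 36, two-sided 5%. Assumed: compound symmetry, equal arms, and a correlation of 0.7 as an alternative.

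**1. The plan's figure reproduces.** Noncentrality = f² × N × m / (1 + (m − 1)ρ) = 0.16 × 36 × 3 / 2 = 8.64 on 1 and 34 df. Power is 0.815; at N = 34 it is 0.791. So 36 is the smallest even total.

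**2. Change from baseline against ANCOVA at 8 weeks.** The noncentrality of the t-test is 10 / (12 × √v × √(4/36)) = 2.5 / √v, where v is the variance relative to SD². For change v = 2(1 − ρ); for ANCOVA v = 1 − ρ².

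| ρ | v, change | power | v, ANCOVA | power |
|---|---|---|---|---|
| 0.5 (plan) | 1.00 | 68% | 0.75 | 80% |
| 0.7 (assumed) | 0.60 | 88% | 0.51 | 92% |
| 0.8 (assumed) | 0.40 | 97% | 0.36 | 98% |

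Estimating the baseline slope costs a factor of about 33/32 in variance, which takes the 80% to about 79%.

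**3. Group main effect.** Suppose 10 points at both follow-ups and none at baseline. The three-visit average differs by (0 + 10 + 10)/3 = 6.7. Its relative variance is (1 + 2 × 0.5)/3 = 0.667. Noncentrality = 6.67 / (12 × 0.816 × 0.333) = 2.04, so power is about 51%. The sizing in step 1 takes f = 0.40, close to (10/12)/2 = 0.417, which is the undiluted difference. It therefore treats the three-visit average as if it carried the whole effect.

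**4. Site.** Adding three sites (2 df) multiplies the variance of the treatment estimate by about (1 − R²)(N − 3)/(N − 5), where R² is the share of outcome variance that site explains.
- At N = 46: 1.05 if R² = 0, 0.94 if 10%, 0.84 if 20%.
- Break-even is R² = 2/(N − 3): 2/43 = 4.7% at N = 46 and 2/33 = 6.1% at N = 36.
- In 20,000 simulated trials with three sites and simple randomisation, the mean error without site adjustment was at most about 0.03 points for R² of 0, 10% or 20%. The cost is precision and uncorrected chance imbalance, not bias.

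**5. Cost of covariates.** The five named variables use 5 to 8 df if education takes 1 to 4 (assumed). At N = 36 the loss from df alone is small: 0.815 falls to 0.811 to 0.808. If none is prognostic, the expected variance inflation (N − 3)/(N − 3 − k) is 33/28 = 1.18 to 33/25 = 1.32. The set of baseline, site and injury level in two groups uses 1 + 2 + 1 = 4 df. If site and injury level explain nothing, they cost 33/30 = 1.10 at N = 36 and 43/40 = 1.075 at N = 46.

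**The case against.** The strongest reply is that a journal article commonly leaves the final covariate set, the site term and any cut-offs to the analysis plan. That stands for detail. It does not cover what the article does commit to, which is baseline as a response level and an adjustment sentence with named variables. The point is that a better method exists than the one stated.

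Several stronger readings are tempting, and the document does not support them.

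- *Baseline is left out altogether.* It is not; it is in the 2 x 3 model. Under a group-by-time test, baseline differences are handled as change, and the loss is one of efficiency.
- *ANCOVA lifts power from 68% to as much as 93%.* At a correlation of 0.7 that compares ANCOVA with an 8-week analysis that ignores baseline, which is not planned. Against change the gain is about 4 points.
- *Site and injury level are excluded.* An illustrative list excludes nothing. The fault is that they are not fixed.
- *Omitting them biases the result.* It does not. In a group-by-time contrast, stable differences between patients also cancel, and only differences in change remain.
- *The covariates use up the degrees of freedom.* The loss from df alone is under one point of power. The larger inflation arises only if they are not prognostic, which is unknown.
- *Arms will often be badly split within sites.* With 15 per site and simple randomisation, a 10:5 or worse split in at least one of three sites has probability 1 − (1 − 0.302)³ = 0.66. Neither input is stated, and small blocks would prevent such splits.
- *Covariates will be picked from the baseline tests.* The article does not link the two; it only leaves that open.

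**Conclusion.** The concern holds as a matter of efficiency and of an unfixed adjusted model. At the plan's own correlation of 0.5, using baseline as a covariate raises 8-week power from 68% to about 80% over change from baseline. The gain shrinks as the correlation rises (88% to 92% at 0.7). If the group main effect, the type of test used for sizing, is read as the treatment effect, power is about 51%, provided the effect is present at both follow-ups. All of these figures are for SCIM III at N = 36 under compound symmetry; the article gives no inputs for rate pressure product.

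For site and injury level the conclusion is weaker. Both are natural candidates on the article's own account, but the gain from site depends on its exceeding about 5% of outcome variance. The document gives no such figure for site or for injury level. A reader should not infer a biased trial from their absence.

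**What to change.** - Make the primary analysis a model of the 8- and 14-week values, with the baseline value of the outcome, site (3 levels) and injury level (grouping fixed in advance) as a closed covariate set.
- State the group contrast, and the visit or visits, that constitute the treatment effect.
- Move sex, education level, BMI, duration and type of injury to one sensitivity model.
- Do not use baseline significance tests to choose covariates.

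The cost is a wording change made before unblinded data are analysed. The baseline outcomes and injury level are already collected, and site is known for every participant. The set takes about 4 df, fewer than the 5 to 8 of the named list. The downside is a slight loss of precision if site or injury level turns out not to be prognostic (up to about 10% in variance at N = 36).
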